### Outcome measurement

#### Baseline variables

The following baseline measures will be collected. Firstly, the sociodemographic status which will include education level, housing status, employment and income details based on the PROGRESS-Plus framework [25] which summarises a number of social stratification factors that potentially impact health opportunities. Secondly, the arthritis status including the symptom duration and the radiographic severity of knee OA based on the Kellgren-Lawrence Scale [26]. Thirdly, the co-morbidities and functional status including the Charlson comorbidity index (CCI) [27], Barthel Index for Activities of Daily Living (BI) [28] and Parker Mobility Score (PMS) [29].

#### Psychosocial variables

The selection of outcome measures was guided by a combination of (I) the themes identified from qualitative work by the study team on local knee OA patient population to identify the potential psychosocial factors that impact knee OA progression [30], (II) a review of international literature, and (III) consultation with local domain experts to ensure local contextualization. The themes identified from the qualitative study (i.e., social support; religion/spirituality; built environment; fear avoidance/kinesiophobia; negative affect, depression/anxiety; and self-image and identity, loss of face) informed the selection of the psychosocial outcomes including social support, religiosity, built environment, fear of movement, etc. [30].

Validated psychosocial questionnaires previously used in OA research (e.g., brief fear of movement (BFOM) [31] and Arthritis Self-Efficacy Scale (ASES) [32], Multidimensional Scale of Perceived Social Support (MSPSS) [33], Chronic pain acceptance questionnaire (CPAQ) will be used for this study. Other outcome measures that have not been administered or validated in the OA population, such as religiosity and built environment, have been adapted from similar questionnaires and refined further by the study team in conjunction with local subject domain experts, contextualizing the questions to the local context to ensure content validity. The set of outcome measures was pilot tested to check for comprehensibility of the items.

#### Clinical, productivity and healthcare utilization outcomes

Recommendations set out by the OA Research Society International (OARSI) for domains of interest pertaining to non-surgical management of OA were adopted (i.e., pain, physical function, activity level, global assessment, and quality of life, etc.) [34, 35] for the clinical outcomes. The primary outcome will be Knee OA and Outcomes Score-12 (KOOS-12) [36]. The KOOS score has previously been validated in Singapore [37]. Other domains include quality of life, global assessment and symptom satisfaction (Tables 2 and 3).

**Table 2 Tab2:** Overview of outcome measures

Baseline Characteristics	Psychosocial Variables		Clinical, Productivity and Healthcare Utilization Outcomes	
**Sociodemographic**	**Depression and Anxiety**	Patient Health Questionnaire-4	**Knee Function**	Knee OA and Outcome Score (KOOS)
**Arthritis status**	**Pain catastrophizing/ fear of movement**	Brief fear of movement	**Quality of Life**	EQ-5D
**Comorbidities and Functional Status**	**Pain experience**	Pain intensity and interference PEG Scale	**Physical Performance**	Gait Speed Time-up-and-Go (TUG) Sit-to-stand (STS) Stair climb
	**Social support**	Multidimensional Scale of Perceived Social Support	**Physical Activity Level**	Step count UCLA activity level
	**Built Environment**^a^	Built environment questionnaire	**Dietary behaviour**	Dietary Questionnaire
	**Chronic Illness Shame**^a^	Chronic Illness Shame Scale	**Global assessment**	Global Perceived Effect
	**Religion and Spirituality**^a^	Religion questionnaire	**Symptom Satisfaction**	Patient Acceptable Symptom Scale
	**Injustice experience**^b^	Injustice Experience Questionnaire	**Cost, Productivity and Healthcare Utilization**	OA Cost and Consequences Questionnaire (including indirect costs and productivity)
	**Self-efficacy**^b^	Arthritis Self-Efficacy Scale	**OA Care Quality**^a^	OA Quality Indicator (OA-QI)

^a^To be administered in phase 1 of study

^b^To be administered in phase 2 of study

**Table 3 Tab3:** Outcome measures

**1. Sociodemographic and clinical data**	
Sociodemographic data	Data of the participants’ age, gender, ethnicity, education level, housing type, marital status, living arrangement, occupation will be collected through self-report
Arthritis status	Clinical variables including arthritis profile, duration, mobility and radiographic severity (Kellegren-Lawrence), and will be collected through a combination of self-report and clinical data extraction
Comorbidity and Functional Status	Charlson comorbidity index [27], Barthel Index for Activities of Daily Living [28] and Parker Mobility Score [29]
**2. Knee function**	
** KOOS-12**	KOOS-12 is a 12-item assessment tool on the participants’ perception of their knee function in the domains of pain, function and daily living, and quality of life [36]. It is measured on a 5-point Likert scale from 0 to 4, with 4 questions in each domain and scored using summative scores in each domain
** Physical Performance**	4 physical performance activities encompass the key domains of functional activities 1. Gait speed 2. Timed up-and-go 3. 4-stair climb test 4. 30-s chair stand
**3. Quality of life**	
The EQ-5D-5L questionnaire, consisting of 5 domains (mobility, self-care, usual activities, pain/discomfort, and anxiety/depression) will be used to assess participant’s quality of life [43]. Each dimension contains 5 levels, from no problem to extreme problems. A 5-digit number which describes the patient’s health state will be generated based on the levels that participants selected for each item. A subsequent index can be computed based on the valuation of the number. A vertical visual analogue scale in the assessment tool also provides for a quantitative measure of participants’ perceived health status	
**4. Depression and anxiety**	
The Patient Health Questionnaire-4 (PHQ-4) is a 4-item questionnaire answered on a four-point Likert-scale to allow the measurement of core sign and symptoms of depression and anxiety [14]. Total score is determined by adding together the scores of each of the 4 items. Scores are rated as normal (0–2), mild (3–5), moderate (6–8), and severe (9–12)	
**5. Pain experience**	
Pain average (P), interference with Enjoyment of life (E), and interference with General activity (G) (PEG) will be used to assess the pain experience [44]. The PEG is a three-item measure derived from the Brief Pain Inventory (BPI) [11, 45] that measures average pain intensity (one item) and pain interference (two items). Patients rate their pain intensity on a numerical rating scale from 0 (no pain) to 10 (pain as bad as you can imagine) and pain interference with enjoyment of life and general activity from 0 (does not interfere) to 10 (completely interferes). A mean score from the three questions will be computed to derive the overall pain impact	
**6. Activity level**	
The UCLA activity score is a 10-point activity scale that assesses activity level based on 10 descriptive activity levels ranging from 1 (i.e., wholly inactive, dependent on others and cannot leave residence) to 10 (i.e., regular participation in impact sports) [38]	
**7. Dietary behaviours**	
A dietary related questionnaire will be used to survey the dietary habits of the participants over the past four months. Questions include the frequency of intake of deep-fried foods, fruits and vegetables, whole grains, and sugar, as well as frequency of over-eating, stress eating, and dietary intention. Responses are reviewed and domain scores will be derived where applicable	
**8. Global and satisfaction**	
** Global Assessment**	The Global Perceived Effect (GPE) scale assesses the patient’s perception of knee OA progression [46]. It is a single item measure with 7-point Likert scale
** Satisfaction with treatment**	Patient Acceptable Symptom Scale (PASS) consists of an item pertaining to the perceived satisfaction of knee function, with a binary yes/no response [47]
** Treatment failure**	Perceived treatment failure will be assessed by an item about the participant’s current condition relating to the failure of the current course of treatment, with a binary yes/no response
**9. Perceived quality of care**	
The OA Quality Indicator (OA-QI) questionnaire seeks to understand the self-reported standard and level of information that the patient was provided with by the healthcare organisation [48]	
**10. Costs**	
Data on the acute health services usage (surgical, medication, others), specialist/medical service usage, community services programme, aids and adaptation will be collected, and the cost on the services related to the knee will be retrieved from the hospital data and the patient-reported cost questionnaire based on the Work Productivity and Activity Impairment Questionnaire (WPAI) and OA Cost and Consequences Questionnaire (OCC-Q)	
**11. Psychosocial**	
** Fear of movement**	Brief Fear of Movement (BFOM) assesses the fear of movement that patient experience [49]. The questionnaire consists of six questions with a 4-point Likert scale ranging from 1 (strongly disagree) to 4 (strongly agree). A summative score of the six questions will be computed, with higher score indicating greater fear of movement
** Self-efficacy**	The Arthritis Self-Efficacy Scale (ASES) assesses how the participants’ confidence in performing certain daily tasks [50]. The summative score indicates the level of self-efficacy the participant has in managing their arthritis
** Pain acceptance**	Chronic Pain Acceptance Questionnaire – 2 (CPAQ-2) is a two-item questionnaire that explores participants’ acceptance of pain in their daily living [51]. Participants rate their response in a seven-point Likert scale range from never true (1) to always true (7)
** Injustice experience**	The Injustice Experience Questionnaire consists of 12 statements that assesses how participants’ perception of injustice in their health condition [52]. The responses will be recorded in a five-point Likert scale range from 0—not at all to 4—all the time, and a total score of all the questions will be computed
** Social support**	The Multidimensional Scale of Perceived Social Support (MSPSS) is used to measure patients’ perception of perceived social support [53]. There were 12 questions in the questionnaire, and each item is rated on a seven-point Likert-type response format (1—very strongly disagree; 7—very strongly agree). A total score is calculated by summing the results for all items. The possible score range is between 12 and 84, the higher the score the higher the perceived social support
** Chronic illness-related shame**	Chronic illness-related shame score (CISS) is a scale specifically focused on shame feelings derived from illness-related experiences [54]. The CISS composed of seven items measured on a five-point Likert scare range from 0 (Never True) to 4 (Always True)
** Religion and spirituality**	The religion and spirituality questionnaire is a 2-item assessment tool developed by the study team to assess the extent that religion and spirituality is a factor in helping the patient cope with their knee condition. The items are rated from 1 (very strongly agree) to 7 (very strongly disagree)
** Built environment**	The built environment questionnaire is a 5-item developed by the study team to assess the participant’s perceptions of accessibility of physical facilities and amenities around their place of residence. This was adapted from the International Physical Activity Questionnaire (IPAQ) environmental module [55]. The items are rated from 1 (very strongly agree) to 7 (very strongly disagree)

The choice of PPMs was based on the recommended OARSI performance test for functional testing in OA [35]. Gait speed timed up-and-go, 4-stair climb test and 30-s chair stand were chosen to encompass the key domains of functional activities from sit-to-stand, walking short distances, stair negotiation and ambulatory transitions. The UCLA activity score is a validated score that is recommended for use in patients with hip or knee OA [38].

The Panel on Cost-Effectiveness in Health and Medicine recommends the use of a societal perspective to ensure that potentially important indirect costs such as productivity and caregiver cost would not be omitted [39]. Cost and healthcare utilization data will be collected via hospital administrative databases and patient-reported questionnaires to estimate direct medical, direct non-medical and indirect costs. Indirect costs include health-related productivity loss due to knee OA [40] from absenteeism and presenteeism, measured with the Work Productivity and Activity Impairment Questionnaire (WPAI) [41]. The scope of the cost data collection was based on the validated OA Cost and Consequences Questionnaire (OCC-Q) [42] and adapted to the Singapore context to ensure that all relevant sources of cost were collected.

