### Study aims

The primary aim is to identify critical psychosocial factors that prognosticate short and long-term clinical outcomes, productivity, and healthcare utilization in patients with knee OA.

The secondary aims areTo explore the mediation and directional relationship between the psychosocial factors with clinical outcome, productivity, and healthcare utilization outcome to support the development of a conceptual frameworkTo explore discordance between self-reported measures (SRM), physical-performance measures (PPMs), objective clinical parameters e.g. radiographic severity in knee OA and the extent to which psychosocial factors predicts the extent of discordance

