#### Handling of missing data

The missing data percentage will be explored and addressed when appropriate. Logistic regression will be used to ascertain the missing data mechanism and the association between the missingness and baseline covariates. Where appropriate, multiple imputation with predictive mean matching (PMM) will be used to predict and impute the missing continuous data based on the observed baseline covariates at each follow-up. On the other hand, the imputation of binary outcomes will be done using the ‘miimputelogit’ package from STATA [57].

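### The stated productivity loss covers only losses while in work, and employment is listed at baseline only, so knee-related work exit has no defined place in the outcome

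*Protocol article*

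**What the plan says.** Under Study aims, the Protocol article sets out to "identify critical psychosocial factors that prognosticate short and long-term clinical outcomes, productivity, and healthcare utilization in patients with knee OA".

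The cost text after Table 3 names the components and the instrument: "Indirect costs include health-related productivity loss due to knee OA [40] from absenteeism and presenteeism, measured with the Work Productivity and Activity Impairment Questionnaire". The same paragraph cites a panel that "recommends the use of a societal perspective to ensure that potentially important indirect costs such as productivity and caregiver cost would not be omitted". It then bases the scope of cost collection on the OCC-Q, "adapted to the Singapore context to ensure that all relevant sources of cost were collected".

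A second instrument also touches productivity. Table 2 lists the "OA Cost and Consequences Questionnaire (including indirect costs and productivity", Table 3 (item 10, Costs) describes a "patient-reported cost questionnaire based on the Work Productivity and Activity Impairment Questionnaire (WPAI) and OA Cost and Consequences Questionnaire (OCC-Q", and the Abstract names both instruments for productivity and healthcare utilization. The items of the adapted questionnaire are not printed.

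Work status appears under Baseline variables as part of "the sociodemographic status which will include education level, housing status, employment and income details", and Table 3 puts occupation in the sociodemographic data. Table 4 ticks demographics at baseline only, but healthcare utilization and productivity costs at baseline, 4, 12 and 24 months.

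Under Handling of missing data, and qualified by a condition that it be appropriate, "multiple imputation with predictive mean matching (PMM) will be used to predict and impute the missing continuous data based on the observed baseline covariates".

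**The concern.** Absence from work and impairment at work exist only for someone who has a job. A person who leaves a job because of the knee has lost all of the baseline working time, yet contributes to neither component. A person who cuts hours because of the knee may show no absence from the shorter schedule. Stopping work, shorter hours and early retirement are mentioned nowhere in the article.

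Two things are at stake. First, mean productivity loss, and hence indirect cost, would be understated. This sits badly with the cited societal perspective, whose purpose is that productivity is not left out. Second, fear of movement, low mood and low self-efficacy may plausibly influence who leaves work. The patients without a value would then not be a random subset, and a factor that acts mainly through work exit would look weaker than it is for productivity.

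An analysis plan can supply a scoring rule later. It cannot recover follow-up work status or the reason for leaving if nobody asked.

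**Working it through.** The article gives no productivity figure to reproduce; its only computed figure is the sample size, which has no bearing here. The check is therefore a reading of the definition, followed by an illustration on assumed inputs.

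**Step 1. Apply the two named components to three people working at baseline.**

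| Patient at 24 months | Absenteeism and presenteeism | Loss due to the knee |
|---|---|---|
| Still working, 30% impaired | 30% | 30% |
| Retired for an unrelated reason | no job to assess | none |
| Gave up the job because of the knee | no job to assess | all baseline working time |

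The second and third patients cannot be told apart by the named components or by work status recorded only at baseline.

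**Step 2. Effect on the mean.** Assumptions, none of them in the article: among baseline workers a share q leaves because of the knee, mean loss among those still working is m, and a knee-related exit counts as 100% loss.

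- Mean including exit: T = (1 − q) × m + 100 × q
- At-work mean, leavers without a value: m
- Relative understatement: (T − m) / T

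| q | m | T | At-work mean | Understated by |
|---|---|---|---|---|
| 2% | 20% | 21.6% | 20% | 7.4% |
| 2% | 30% | 31.4% | 30% | 4.5% |
| 5% | 20% | 24.0% | 20% | 16.7% |
| 5% | 30% | 33.5% | 30% | 10.4% |
| 10% | 20% | 28.0% | 20% | 28.6% |
| 10% | 30% | 37.0% | 30% | 18.9% |
| 15% | 20% | 32.0% | 20% | 37.5% |
| 15% | 30% | 40.5% | 30% | 25.9% |

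For q = 10% and m = 20%: T = 0.9 × 20 + 10 = 28, and (28 − 20) / 28 = 28.6%. If an exit is valued at v instead of 100, T − m = q × (v − m). The direction holds whenever an exit is valued above the average at-work loss.

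**Step 3. Effect on an association.** Simulation of 1,000,000 baseline workers with a standard normal factor. At-work loss is 25 plus 2 or 4 points per SD of the factor, with noise SD 20, limited to 0-100. Exit is logistic with odds ratio 1.5 or 2.0 per SD and 10% leaving overall. Slopes are in points per SD.

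| At-work effect | Exit odds ratio | Slope including exit | Slope among those still working |
|---|---|---|---|
| 2 | 1.5 | 4.2 | 1.8 |
| 2 | 2.0 | 6.0 | 1.8 |
| 4 | 1.5 | 5.8 | 3.6 |
| 4 | 2.0 | 7.5 | 3.5 |

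The at-work slope is a fair answer to a narrower question (the inputs of 2 and 4 shrink slightly because loss is cut off at 0). What it lacks is the part of the factor's effect that runs through leaving work.

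**Step 4. Imputation.** If predictive mean matching were applied to leavers, the donors would be people with an observed at-work value, that is, people still working. For a leaver that value is undefined rather than unobserved, so matching on baseline covariates would not restore the lost work.

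**The case against.** The strongest reply is that the article does not limit itself to the WPAI. It says indirect costs include these losses, adapts the OCC-Q so that no relevant cost is missed, labels the OCC-Q as covering productivity, and builds the patient questionnaire on both instruments. That questionnaire is given at every visit and may already ask about current work and why it changed. Printing items is not an article's job, and scoring rules commonly sit in the full protocol or analysis plan.

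Much of this stands. It cannot be said that productivity is derived only from the two components, or that follow-up work status is not collected. A reader might also infer that a leaver is scored as having no loss, so that the worst outcome counts as none. The article does not support that: it gives no rule for people not in work, neither zero, exclusion nor missing. Nor does it say that at-work loss will be imputed for them, since imputation is to be used only where appropriate.

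What does not fall is the definition itself. The word "include" governs indirect costs. Within productivity loss, absenteeism and presenteeism are the only sources named, and measurement is assigned to the WPAI. The instrument's title also mentions activity impairment, but the text uses it for these two work losses. Even if the OCC-Q records a work exit, nothing says that it enters the productivity outcome.

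The reply is also right on weight. The primary outcome is KOOS-12, and productivity is one of several domains in the aim.

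**Conclusion.** The point holds in a limited form. The stated definition names only losses that occur in work, lists employment at baseline only, and so leaves knee-related work exit without a defined place, unless an unprinted OCC-Q item records it and is carried through. Followed literally, the productivity analysis is conditional on staying in work, and that selection is plausibly related to the factors under study. The expected direction is understated loss and weaker associations.

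The size is unknown. The article gives no share employed (patients are 45 or over with no stated upper limit), no exit rate and no mean loss. The 4.5-37.5% understatement and the slopes above rest wholly on assumed inputs and on valuing an exit as full loss. At 2% leaving, the mean changes by less than 2 percentage points. A reader might go further and expect an association to reverse; that would need leavers to be scored zero, which the article does not say. This is a cheap improvement, not a flaw in the primary outcome.

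**What to change.** - Among those working at baseline, define productivity loss at each follow-up as absenteeism plus presenteeism plus baseline working time lost by stopping or reducing work because of the knee.
- If the adapted OCC-Q already has such an item, say so and carry it into the outcome. Otherwise add current work status and the reason for any change to the existing cost questionnaire at 4, 12 and 24 months.
- Do not impute at-work loss for people who are not in work.
- Report the at-work-only result alongside, labelled as conditional on still working.
- State the value given to lost hours (for example, all baseline hours for a knee-related exit) and vary it in a sensitivity analysis.

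Cost: one or two items in a questionnaire already given at every visit, and one derivation rule. The drawbacks are a little more respondent burden, reliance on the patient's own reason for leaving work, and a valuation of lost hours that remains an assumption.

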#### Outcome measures timepoints

Upon baseline outcome measure taking, participants will be followed up at 4 months, 12 months, and annually after that. To reduce respondent fatigue and keep questionnaire burden to the minimum, psychosocial variables will be administered in two phases (Table 2) with a core set of outcome measures collected at all time points. In addition, certain psychosocial variables eg. built environment, that are not anticipated to change significantly over time will only be taken at baseline (Table 4).

**Table 4 Tab4:** Data collection at different time points

Measure	Baseline	4 month	12 month	24 month
